## Abstract

**Background:**

Transcatheter aortic valve implantation via the transfemoral route (TF-TAVI) is commonly performed as a treatment for severe aortic stenosis (AS) in patients at high surgical risk. Pre-deployment balloon aortic valvuloplasty (BAV) has generally been considered an essential step for preparing the valve landing zone for receipt of the prosthesis. However, there is little evidence supporting the clinical value of BAV, while several associated complications have been documented. This has provoked several groups to evaluate the feasibility and safety of omitting BAV form the TF-TAVI procedure (direct TF-TAVI), with encouraging results. However, studies comparing the clinical outcomes of direct TF-TAVI to standard TF-TAVI are lacking.

**Methods:**

EASE-IT TF is a prospective, observational, two-armed, multicentre registry designed to gather data on procedural aspects, adverse events and survival rates associated with direct TF-TAVI using the Edwards SAPIEN 3 balloon-expandable prosthesis.

**Discussion:**

EASE-IT-TF data will be analysed firstly to determine the risks and benefits associated with direct TF-TAVI vs. standard TF-TAVI, and secondly to identify associations between patient variables and specific outcomes. This may assist identification of patients who stand to benefit from direct TF-TAVI, therefore contributing to clinical reductions in TF-TAVI-associated morbidity and mortality rates in high-risk AS patients.

**Trial registrations:**

Clinictrials.gov: NCT02760771

## Background

Until recently, pre-dilation of the stenosed aortic valve using an expandable balloon (pre-deployment balloon aortic valvuloplasty; BAV) has been deemed an essential step for facilitating the crossing of the aortic annulus, reducing radial counterforce, and permitting greater prosthetic heart valve (PHV) expansion during transcatheter aortic valve implantation (TAVI) [1], though there is little proof of this in the literature. BAV may also permit early evaluation of cusp positioning, calcification, and the potential for balloon slippage during the successive valve landing [2]. Conversely, there are several problems associated with BAV, including transient coronary, cerebral, and renal ischemia, haemodynamic instability and systemic inflammatory response syndrome as a result of the need for rapid ventricular pacing (>180 bpm for up to 30 s) [2]; conduction disturbances requiring permanent pacemaker implantation (PPI) [3, 4]; coronary occlusion; tamponade; profound hypotension; aortic regurgitation; and displacement of fragments from the valve increasing stroke risk [4–7]. With this in mind, modification of the TAVI procedure to omit the BAV step has been investigated in several clinical studies for a variety of access routes, and generally demonstrated to be feasible and safe without compromising procedural success [1, 5, 8–14].

Several pilot studies in high surgical risk patients undergoing TF-TAVI without prior BAV (direct TF-TAVI) have been published to date. An early pilot study by Grube et al. in 60 consecutive patients undergoing direct TF-TAVI with the Medtronic CoreValve PHV described a 96.7 % procedural success rate, with in-hospital mortality, stroke, major vascular complication, and myocardial infarction (MI) rates of 6.7, 5, 10, and 0 %, respectively [1]. Concurrently, a similar pilot study by Mendiz et al. using the same PHV demonstrated that direct TF-TAVI in 51 patients led to a procedural success rate of 94.2 %, with PPI, stroke and all-cause mortality rates of in 27.5, 3.9, and 3.9 % at 30 days [11]. Most recently, a larger retrospective study enrolling 163 patients found that direct TF-TAVI with the SAPIEN 3 PHV was feasible in 94.5 % of cases, and had an all-cause mortality rate of 3.7 % at 30 days [10]. BAV was required to overcome crossing difficulties in only 5.5 % of patients, who were generally older, had a higher calcium score, higher transvalvular gradients, and smaller AVA. Thus, pilot studies have demonstrated the feasibility of direct TF-TAVI in the majority of standard TF-TAVI candidates; though suggest that further studies to identify characteristics of patients for whom the technique is most appropriate would be useful.

Early, small comparative studies found that compared to standard TF-TAVI, direct TF-TAVI resulted in higher success rates (85 % vs. 64 %), a significantly lower incidence of moderate-to-severe paravalvular leak (9 % vs. 33 %) [12], reduced radiation dosage (42.0 vs. 56.6 Gy cm^2^), and reduced contrast agent volume (92.2 vs. 112 mL) [13]. Bijkulic et al. found, guided by diffusion-weighted magnetic resonance imaging, that the implantation of a balloon-expandable aortic valve without versus with prior BAV, although performed with a shorter procedure time and lower contrast volume, is associated with a significantly higher volume of cerebral ischemic lesions [15]. A later, case-matched analysis in 52 patients using Edwards SAPIEN PHVs found no significant difference between direct TF-TAVI and standard TF-TAVI in terms of success rate (96.2 % vs. 92.3 %), all-cause mortality at 30 days (both 7.7 %), disabling stroke (3.8 % vs. 7.7 %) or moderate-severe paravalvular leak (0 % vs. 7.7 %); though did document significantly lower procedural times (60 vs. 70 min), fluoroscopy time (13.3 vs. 17.8 min), and contrast agent volume (118.7 vs. 153.0 mL) for direct TF-TAVI [8]. However, the insufficient statistical power and unsatisfactory study design of the aforementioned studies prevent firm conclusions being drawn. One larger study by Islas et al. in 249 consecutive patients undergoing TF-TAVI was published recently, and found that direct TAVI resulted in significantly shorter procedural durations (108.5 vs. 133.7 min), reduced rates of PPI (6.3 % vs. 14.1 %), procedure-related mortality, and 30-day mortality (both 2.5 % vs. 11.8 %) [16]. While these results are encouraging, it should be noted that group assignment was based on pre-defined transesophageal echocardiographic criteria potentially biasing patient populations, the study was monocentric, and employed two different PHVs (only 106 patients received the Edwards SAPIEN PHV and 143 patients the CoreValve). Thus, findings should be interpreted with care. Considered together, early comparative studies suggest that direct TF-TAVI may offer several advantages over standard TF-TAVI, though carefully designed, multi-centric, large-cohort studies are clearly required.

To the best of our knowledge, no large registry, fully-prospective studies comparing direct TF-TAVI to standard TF-TAVI with the Edwards SAPIEN PHVs have been published to date. We have therefore designed a two-armed, controlled-cohort, observational, multicentre registry (EASE-IT TF) to investigate the clinical implications of BAV in TF-TAVI using the balloon expandable Edwards SAPIEN 3 PHV. Data on procedural aspects, adverse events and mortality will be used to identify differences in operative outcomes when BAV is performed or omitted. Possible associations between patient variables and these outcomes will then be identified.

## Methods/design

This prospective, non-randomised, non-interventional controlled cohort study evaluating the safety and efficacy of the Edwards SAPIEN 3 PHV in standard TF-TAVI vs. direct TF-TAVI is based on EASE-IT TF: a two-armed, observational registry containing data from 10 German sites. Ethic committee approval was obtained from the appropriate ethics committee in writing prior to patient an enrolment. We aim to enrol and average of 20 patients per site, generating a minimum study population of 200. All patients are required to provide a signed informed consent form (ICF) prior to enrolment.

### Site selection

Selected sites must have prior experience of TF-TAVI implantations and the proven capacity to enrol at least 2 patients per month. Additionally, independently of inclusion in the registry, all participating sites must have received the following training for implantation of the Edwards SAPIEN 3: 1) instructions for use (IFU) provided by the manufacturer, 2) exhaustive fundamentals training (i.e., device preparation, didactic sessions, simulator training and case observations), and 3) on-site training as per the Edwards Standard Operating Procedure.

### Patient selection

In order to be included in the study, patients are required to meet all of the following criteria: 1) indication for TF-TAVI according to the IFU for the Edwards SAPIEN 3 PHV, 2) age ≥18 years, 3) signed ICF. All patients meeting any of the following criteria will be excluded from the study: 1) contraindications for TAVI via the TF access route according to the Edwards SAPIEN 3 IFU, 2) logistic Euro-SCORE I >40 %, 3) mitral or tricuspid valvular insufficiency > grade II, 4) uncontrolled atrial fibrillation (no rhythm control established), 5) left ventricular or atrial thrombus identified via echocardiography, 6) previous aortic valve replacement, 7) mobile structures on leaflets, 8) requirement for a cerebral protection device, and 9) high probability of non-adherence to follow-up requirements based on social, psychological or medical grounds. So as to avoid influencing investigator decision to perform TF-TAVI with or without BAV, enrolment in the register will occur after this choice had already been made, and a 1:1 ratio will not be strictly pursued (Fig. 1). Reasons for this decision and any subsequent changes will be systematically documented. Subjects withdrawing consent will be omitted from the registry and not replaced.

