### Outcome measures

The primary outcome measure is the combined rate of all-cause mortality, stroke, non-fatal MI, acute kidney injury (AKI), and PPI between commencement of the TAVI procedure and 30 days (±7 days) post-intervention. Secondary outcome measures are each of the aforementioned factors making up the primary outcome considered separately at 30 days (±7 days) and 6 months (±16 days) post-TAVI, procedure time, duration of radiation exposure, volume of contrast agent used, and rate of aortic root rupture. A further secondary outcome measure is the combined rate of all-cause mortality, stroke, non-fatal MI, AKI, and PPI up to 6 months (±14 days) post-TAVI.

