### Statistics

To achieve a statistical power of 80 %, the estimated sample size needed to detect an absolute risk reduction of 13 % at 30 days post-TAVI was 180 evaluable patients. This calculation was based on the 30-day event rates reported by a previous study on direct TF-TAVI by Grube et al. [1]. In order to accommodate an approximate drop out rate of 10 % (20 patients) during the first 30 days, a final necessary sample size of 200 patients was established.

Analysis for all patients in the registry will be performed from an intention-to-treat perspective. The collected data will be presented and summarised using descriptive statistics. Categorical variables will be reported as frequency distributions, while continuous variables will be reported as mean (± standard deviation) and median (range) values. Where appropriate, actuarial probability and linearised rates may be used to report on adverse events. Survival (and adverse event outcomes, where appropriate) will be analysed using the Kaplan-Meier method.

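### Omitting patients who withdraw consent lets the intention-to-treat set depend on what happens after the procedure, and may bias the 30-day composite

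*Protocol article*

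**What the plan says.** Four statements in the protocol article bear on this point.

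- Patient selection, on withdrawal: "Subjects withdrawing consent will be omitted from the registry and not replaced". The article does not say what happens to data already collected.
- Patient selection, on the decision for or against balloon valvuloplasty: "enrolment in the register will occur after this choice had already been made". The strategy is therefore known before a patient enters the registry.
- Outcome measures: the primary composite (death, stroke, non-fatal myocardial infarction, acute kidney injury, permanent pacemaker) is counted "between commencement of the TAVI procedure and 30 days (±7 days) post-intervention".
- Statistics: "Analysis for all patients in the registry will be performed from an intention-to-treat perspective". The same section sizes the study on 180 evaluable patients and allows for an "approximate drop out rate of 10 % (20 patients) during the first 30 days". It names the Kaplan-Meier method for survival and, where suitable, for adverse events.

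Table 1 has adverse events recorded at the intervention, at discharge, at 30 days and at 6 months.

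**The concern.** Consent is given before the procedure and can be withdrawn at any later time, including after a primary event has been recorded. If such a patient is then left out of the registry, the event goes too. The analysed set would be fixed partly by what patients decide after treatment, and that decision may depend on how treatment went. Keeping every enrolled patient in the group first chosen is meant to prevent this.

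If withdrawal is related to outcome, the event rate in each arm is biased. If that relation or the share withdrawing differs by arm, the comparison is biased as well. A patient who has died can no longer withdraw, so removal can only take out recorded non-fatal events. That could change the mix of components within the composite. Allocation is by physician choice and need not be 1:1, so a few removals weigh more in a smaller arm.

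**Working it through.** **The plan's own figure.** 180 evaluable patients and 10 % drop-out give 180 / (1 − 0.10) = 200, and 200 × 0.10 = 20 patients. This reproduces. Drop-out without replacement is already covered, so the point does not touch the sample size. I take the 180 as given.

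**Scale.** With equal arms of 90 evaluable patients, the 13-point target is 0.13 × 90 = 11.7, or about 12 events.

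**Formula.** Let q be the share of an arm that is omitted, and let Δ be the event risk of omitted patients minus that of patients who stay. The full-arm rate exceeds the rate in those who stay by q × Δ. With the same Δ in both arms, omission shifts the risk difference by

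(q_a − q_b) × Δ.

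**Illustration 1.** Assumed: arms of 100 and Δ = 25 points. Neither the split of withdrawals nor Δ is in the documents.

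| Omitted, arm a vs arm b | Patients omitted | Shift | Share of 13 points |
|---|---|---|---|
| 10 % vs 10 % | 20 | 0 × 0.25 = 0 | 0 % |
| 2 % vs 0 % | 2 | 0.02 × 0.25 = 0.5 points | 4 % |
| 15 % vs 5 % | 20 | 0.10 × 0.25 = 2.5 points | 19 % |
| 20 % vs 0 % | 20 | 0.20 × 0.25 = 5 points | 38 % |

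The last two rows use up the whole allowance of 20 as consent withdrawals, and the last row puts all of them in one arm.

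**Illustration 2.** Assumed: 100 per arm, the same true rate in both arms, and w patients omitted from one arm only. If every omitted patient had an event, the observed rate in that arm is (events − w) / (100 − w).

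- True rate 30 %: w = 2, 5, 10 gives 28/98 = 28.6 %, 25/95 = 26.3 %, 20/90 = 22.2 %. The spurious difference is 1.4, 3.7 or 7.8 points.
- True rate 19 %: w = 2, 5, 10 gives 17/98 = 17.3 %, 14/95 = 14.7 %, 9/90 = 10.0 %. The spurious difference is 1.7, 4.3 or 9.0 points.

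If 60 % of the omitted patients had an event instead, w = 5 and w = 10 give 1.6 and 3.3 points at a 30 % rate ((30 − 3)/95 = 28.4 %; (30 − 6)/90 = 26.7 %). At a 19 % rate they give 2.2 and 4.6 points ((19 − 3)/95 = 16.8 %; (19 − 6)/90 = 14.4 %).

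The result therefore runs from zero, when withdrawals are balanced, to several points, when they are one-sided and closely tied to events. The documents do not say where in that range the study will fall.

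**The case against.** **The two sentences fit together.** The analysis covers patients in the registry, and withdrawn patients are no longer in it. A reader might infer a contradiction, but the text does not support that. In a non-randomised registry, intention-to-treat can also mean mainly that patients are analysed by the strategy chosen beforehand, even if it changes during the procedure. This stands as a point about wording. It does not remove the concern, because defining patients out after treatment is what causes the problem.

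**Erasure is an inference.** The sentence could mean only that no further data are collected. Complete removal is the plainer reading, since what is omitted is the subject and not later visits, but it is not certain. If the milder meaning is intended, one sentence settles it.

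**The detail may belong elsewhere.** The full protocol, the analysis plan and the consent form are not shown, and silence in an article would be no finding. Here the article is not silent: it states a rule, and that rule as worded removes patients. Removal may be a condition of consent, so any fix must allow for it.

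**No withdrawal figure exists.** A reader might take the 10 % as the expected withdrawal rate. It covers all drop-out in the first 30 days, and no share is assigned to consent withdrawal. That a material number will withdraw therefore does not follow from the documents, and the splits and the 25-point excess risk are assumptions. This objection stands in full.

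**Censoring is not a complete cure.** It keeps events recorded before withdrawal, but for later ones it assumes that withdrawal is unrelated to risk, which is the very thing in doubt. This also stands, and is why a bound is needed.

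**Conclusion.** The point holds as a departure from the intention-to-treat principle that should be corrected. It rests on the plain reading of the withdrawal rule. On that reading, the primary analysis covers only patients who did not withdraw, a group settled partly after the procedure and possibly after an event. Bias in the 30-day composite is possible if withdrawal is related to outcome and differs by arm.

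Its size is unknown. Shifts of about 2.5 to 5 points against the 13-point target are illustrative. They are at the upper end for the number withdrawing, because they count all 20 expected drop-outs as consent withdrawals. They are not a strict maximum: if every omitted patient had an event and all came from one arm, 10 omissions would give 7.8 to 9.0 points. With few or balanced withdrawals the shift is close to zero. The documents do not support saying that the comparison will be biased by any stated amount, or that the sample size is wrong.

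**What to change.** Replace the withdrawal sentence under Patient selection with a rule along these lines:

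- Patients who withdraw consent are not replaced. Data collected up to withdrawal are kept where consent allows and are analysed by the strategy chosen before the procedure.
- Follow-up is censored at withdrawal.
- Data are erased only on the patient's explicit request.
- Withdrawals and erasures are reported by arm and by timing relative to the procedure. A withdrawal before the procedure cannot hide a primary event, whereas a later one can.

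Add one sensitivity analysis of the 30-day composite. Withdrawn patients whose 30-day outcome is unknown are counted first as events and then as non-events, including the opposite assignment in the two arms. The bound spans the unknown share of each arm: 10 unknown outcomes in an arm of 100 give 10 points for that arm's rate. If erasures occur, their counts by arm enter the same bound.

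**Cost.** One sentence in the protocol and one in the analysis plan, possibly a line in the consent form, and a small sensitivity analysis. The consent form is not shown, so whether it needs changing cannot be settled here. The sample size stays at 200.

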**Fig. 1 Fig1:**
[figure not shown]
Diagram of registry design, procedures and stages

### TF-TAVI procedure

Investigators are free to perform TF-TAVI using the Edwards SAPIEN 3 PHV according to locally-adopted techniques. Patients in the standard TF-TAVI group will undergo the procedure with pre-deployment BAV, while those in the direct TF-TAVI group will undergo the procedure without pre-deployment BAV.

### Outcome measures

The primary outcome measure is the combined rate of all-cause mortality, stroke, non-fatal MI, acute kidney injury (AKI), and PPI between commencement of the TAVI procedure and 30 days (±7 days) post-intervention. Secondary outcome measures are each of the aforementioned factors making up the primary outcome considered separately at 30 days (±7 days) and 6 months (±16 days) post-TAVI, procedure time, duration of radiation exposure, volume of contrast agent used, and rate of aortic root rupture. A further secondary outcome measure is the combined rate of all-cause mortality, stroke, non-fatal MI, AKI, and PPI up to 6 months (±14 days) post-TAVI.

### Data collection

Data on enrolled patients will be collected via electronic case report forms (eCRFs) using registry identification numbers rather than names, to protect identity. eCRFs will be completed for the visit prior to implantation, on the day of implantation, and at follow-up visits 30 ± 7 days and 6 months (±14 days) post-implantation, and signed at the earliest opportunity by either the investigator or designated responsible party (Table 1). The results of pre-TAVI echo and CT assessment will be documented as well as potential reasons for or against opting for BAV in a given patient. Additionally, reports of device-related serious adverse events or death must be provided within 48 h of occurrence. Up to 2 sites (20 %) will be randomly selected for monitoring purposes following completion of data collection, and subjected to source data verification (expected to be 100 % for stroke, life-threatening or major bleeding, renal failure, vascular and valve complications, PPI and mortality).

**Table 1 Tab1:** Assessments

Parameter	Admission	Intervention	Discharge	30d FU	6 Mo FU
Inclusion/Exclusion criteria	X				
Demographics	X				
Diagnosis of valve disease	X				
Echocardiography	X				
Computed Tomography	X				
Symptoms	X			X	X
Cardiac baseline characteristics	X				
ECG	X		X		
Comorbidities	X				
Risk scores	X				
Prior cardiovascular intervention	X				
Current medications	X		X	X	X
Interventional details		X			
Interventional results		X			
AE		X	X	X	X
Hospitalization duration			X		
Creatinine value	X		X		X
Early safety/Clinical efficacy				X	X

### Statistics

To achieve a statistical power of 80 %, the estimated sample size needed to detect an absolute risk reduction of 13 % at 30 days post-TAVI was 180 evaluable patients. This calculation was based on the 30-day event rates reported by a previous study on direct TF-TAVI by Grube et al. [1]. In order to accommodate an approximate drop out rate of 10 % (20 patients) during the first 30 days, a final necessary sample size of 200 patients was established.

Analysis for all patients in the registry will be performed from an intention-to-treat perspective. The collected data will be presented and summarised using descriptive statistics. Categorical variables will be reported as frequency distributions, while continuous variables will be reported as mean (± standard deviation) and median (range) values. Where appropriate, actuarial probability and linearised rates may be used to report on adverse events. Survival (and adverse event outcomes, where appropriate) will be analysed using the Kaplan-Meier method.

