A frequently observed clinical complication of TAVI is AKI, which has been documented in around 16 % of patients and is associated with poor prognosis [19–22]. One factor that may contribute to AKI is the volume of contrast agent used. Van Linden et al. reported a significant correlation between intraoperative contrast agent volume and postoperative AKI in 270 consecutive patients undergoing TA-TAVI with the Edwards SAPIEN PHV [22]. In particular, use of >99 ml of contrast agent was an independent predictor of AKI. Concurrently, a study by Yamamoto et al. in a cohort of 415 elderly TF-TAVI patients found that subjects experiencing post-procedural AKI had been exposed to greater contrast agent doses, and multivariate analysis confirmed the association [21]. Furthermore, a study by Madershahian et al. including 50 patients with pre-existing renal impairment undergoing TA-TAVI with the Edwards SAPIEN PHV found a significantly greater prevalence of acute contrast-induced nephropathy in patients receiving >100 mL contrast agent compared to those receiving <100 mL (69.2 % vs. 41.7 %, respectively) [23]. It therefore appears that reducing contrast agent volume may reduce AKI rates. Importantly, several studies report that direct TAVI significantly reduces contrast agent volumes [8, 13], indicating the potential for this to translate into reduced AKI. Again, results from the EASE-IT TF registry will help to clarify this idea.

Conduction disturbances requiring PPI have been reported to occur in 13–25 % of patients undergoing TAVI [3, 24]. In PARTNER, patients requiring PPI had longer postoperative hospitalisation times (7.3 days vs. 6.2 days), higher frequencies of repeat hospitalisations up to 1 year (23.9 % vs. 18.2 %) and increased mortality or repeat hospitalisation up to 1 year (42.0 % vs. 32.6 %) [25]. Therefore, reducing PPI requirement is clearly desirable. In a study by Gensas et al., BAV was identified as an independent predictor of PPI requirement [3]. Concurrently, findings by Grube et al., Fiorina et al. and Islas et al. suggest that PPI rate is lower in patients undergoing direct TF-TAVI compared to standard TF-TAVI (11.7 % vs. 27.8 %, 5.5 % vs. 15.5 %, and 6.3 % vs. 14.1 %, respectively). Conversely, Conradi et al. found no significant difference in PPI rate between the two procedural variants (both 15.4 %). Therefore, the effect of BAV on PPI requirement requires additional investigation, which the EASE-IT TF study will provide.

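### The stated 80 % power for a 13-point reduction with 180 patients does not reproduce at a 5 % alpha from the rates the article prints for its named source study

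*Protocol article*

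**What the plan says.** The sample-size paragraph (Protocol article, Statistics) opens with "To achieve a statistical power of 80" % and continues that "the estimated sample size needed to detect an absolute risk reduction of 13 % at 30 days post-TAVI was 180 evaluable patients". On the inputs it says: "This calculation was based on the 30-day event rates reported by a previous study on direct TF-TAVI". Allowing about 10 % dropout, it arrives at 200 patients. It prints no alpha, sidedness, test or arm rates, and does not name the endpoint. Under Outcome measures, the primary outcome is the 30-day composite of death, stroke, non-fatal MI, AKI and permanent pacemaker implantation (PPI).

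For the source study, a CoreValve pilot in 60 patients, the article prints two sets of figures:

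- Background: "with in-hospital mortality, stroke, major vascular complication, and myocardial infarction (MI) rates of 6.7, 5, 10, and 0 %, respectively".
- Discussion: PPI rates for direct vs standard TF-TAVI from three studies, "11.7 % vs. 27.8 %, 5.5 % vs. 15.5 %, and 6.3 % vs. 14.1 %, respectively". The first pair, 11.7 % vs 27.8 %, belongs to the source study.

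The Discussion also mentions "AKI, which has been documented in around 16 % of patients", a figure for TAVI in general. On allocation, Patient selection says "a 1:1 ratio will not be strictly pursued".

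**The concern.** For a fixed absolute difference, the power of a two-proportion comparison depends heavily on the level of the rates. A 13-point gap is much easier to detect at 17 % vs 4 % than at 36 % vs 23 %. A total of 180 for 13 points therefore implies low composite rates. The composite has five components, and one of them, PPI, is already at 11.7 % in the direct arm of the study named as the source.

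If the true rates are higher than the calculation implies, the registry will be reported as an 80 %-power comparison when its chance of detecting its own target is clearly smaller. The article faults earlier comparative studies for insufficient power (Background), so readers will take the stated power at face value.

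**Working it through.** **Inputs.** The 13-point difference, 180 evaluable patients and 80 % power come from Statistics. The source study's death 6.7 %, stroke 5 % and MI 0 % come from Background, and its PPI 11.7 % (direct) from the Discussion. AKI at 16 % comes from the Discussion and is not specific to that study. Assumed because not stated: the endpoint sized is the primary composite, the split is 1:1 (90 per arm), and alpha is 5 %, taken both two-sided and one-sided.

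**Formulas** (normal approximation, pooled variance under the null). Let C be the standard arm, D the direct arm and p̄ their mean.

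- n per arm = [z_α·√(2p̄(1−p̄)) + 0.842·√(pC(1−pC) + pD(1−pD))]² / 0.13²
- Power = Φ[(0.13 − z_α·SE0)/SE1], with SE0 = √(2p̄(1−p̄)/90) and SE1 = √((pC(1−pC) + pD(1−pD))/90)
- z_α = 1.960 (two-sided 5 %) or 1.645 (one-sided 5 %)

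**Step 1: the plan's own figure.** The dropout step reproduces: 180/(1 − 0.10) = 200. Solving the first formula for a total of 180 gives about 17.5 % vs 4.5 % two-sided (total 179.5) and about 21 % vs 8 % one-sided (total 179.3). A continuity correction moves the rates lower: about 15.5 % vs 2.5 % two-sided and 18 % vs 5 % one-sided.

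**Step 2: the floor.** A composite cannot be rarer than its commonest component. With PPI at 11.7 %, the direct-arm composite is at least 11.7 %, and a 13-point reduction then puts the standard arm at 24.7 % or more. Every solution in step 1 lies below this floor. The step needs no AKI figure and no assumption about overlap.

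**Step 3: power at the floor.** For 24.7 % vs 11.7 %, p̄ = 0.182, SE0 = 0.0575 and SE1 = 0.0567.

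- Two-sided: (0.13 − 1.960 × 0.0575)/0.0567 = 0.305, and Φ = 0.62.
- One-sided: (0.13 − 1.645 × 0.0575)/0.0567 = 0.62, and Φ = 0.73.

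**Step 4: higher composites from the printed rates.**

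- No overlap, no AKI: 6.7 + 5 + 0 + 11.7 = 23.4 %.
- AKI at 16 % added, components independent: 1 − 0.933 × 0.95 × 0.883 × 0.84 = 34.3 %.

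| Standard vs direct | Power two-sided 5 % | Power one-sided 5 % | Total N for 80 % (two-/one-sided) |
|---|---|---|---|
| 24.7 vs 11.7 % (full overlap) | 62 % | 73 % | 276 / 216 |
| 36.4 vs 23.4 % (no overlap, no AKI) | 48 % | 60 % | 388 / 306 |
| 47.3 vs 34.3 % (AKI 16 % assumed) | 43 % | 55 % | 448 / 352 |

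**Step 5: alternative readings.**

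- Standard arm set at the source study's PPI rate of 27.8 % (27.8 vs 14.8 %): 57 % two-sided, 69 % one-sided.
- The pilot's summed 23.4 % used as the standard-arm rate (23.4 vs 10.4 %): about 65 % and 76 %.
- One-sided 10 % alpha (z = 1.282): 84 % at 24.7 vs 11.7 % and 80.5 % at 27.8 vs 14.8 %, but 74 % at 36.4 vs 23.4 %.
- 2:1 split at 36.4 vs 23.4 %, two-sided: 45 % with 60 standard and 120 direct, 42 % the other way round.

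**Step 6: what 90 per arm can show.** Solving the power formula for the difference at 80 % (two-sided) gives about 16 points at a standard-arm rate of 25 % and about 20 points at 47 %. The 95 % CI half-width, 1.96 × SE1, is 11.1, 13.2 and 14.2 points in the three rows of the table.

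**The case against.** The strongest reply is that the article condenses a fuller protocol. Alpha, sidedness, test and arm rates may be given there, and their absence from the article is not itself an error. The source study may report a 30-day composite that the article does not print. Everything below the 62 % figure is a composite assembled here, and the 43 % row borrows its AKI rate from other studies. A one-sided 10 % alpha would rescue the claim at the lowest rates. All of this stands, and it rules out a single headline such as 43–62 %. It does not restore 80 % at a 5 % alpha, because the floor rests only on a rate the article prints for the study it names.

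A reader might infer further faults that the documents do not support:

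- **In-hospital vs 30-day.** Background gives in-hospital rates, while Statistics refers to 30-day rates. One study can report both, so there is no contradiction. Within the same patients, cumulative 30-day rates could not be lower than in-hospital rates.
- **No AKI rate for the source study.** A condensed article may leave this out.
- **CoreValve as the planning source.** The article's criticism of mixed devices concerns a comparison that pooled two valves, not planning from data on one.
- **Unequal allocation.** The limitations section already concedes that it may reduce power.
- **A null result read as equivalence.** Nothing in the article says it would be read that way.

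**Conclusion.** The power statement is wrong as written at a 5 % alpha, given the rates the article prints for its own source. At most, 180 evaluable patients give about 62 % power two-sided or 73 % one-sided for a 13-point reduction when the direct-arm composite sits at its 11.7 % floor. Under the higher composites considered, the figure falls to about 43 % or 55 %.

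The upper figures rest on a 1:1 split, on the primary composite being the endpoint sized, and on the source study's PPI rate applying to the direct arm. The lower figures also rest on non-overlapping or independent components and, for the last row, on AKI at 16 %. It would go too far to say that the registry's power is 43–62 % without these conditions, or that its sample size must rise. The documents support neither.

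**What to change.** Keep N = 200 and rewrite the sample-size paragraph. State the endpoint, the 30-day composite rate assumed in each arm (including AKI), alpha, sidedness, test and assumed split, and recompute from those. Replace the claim of 80 % power for 13 points with:

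- the power achieved for 13 points: under the assumptions above, about 43–62 % two-sided or 55–73 % one-sided at 1:1, and generally lower at 2:1;
- the difference detectable at 80 % power: about 16–20 points two-sided for standard-arm rates of 25–47 %;
- the expected 95 % CI half-width: about ±11 to ±14 points.

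If the full protocol used other rates or a more lenient alpha, print those and the figure that follows from them. The sponsor's own inputs should replace the ranges given here.

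The cost is a reworded paragraph and a less favourable stated power. No patients, visits or data are added.
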